# Effect of provision of an integrated neonatal survival kit and early cognitive stimulation package by community health workers on developmental outcomes of infants in Kwale County, Kenya: study protocol for a cluster randomized trial

**DOI:** 10.1186/s12884-016-1042-5

**Published:** 2016-09-08

**Keywords:** Child development, Neonatal mortality, Kenya, Community health workers, Stimulation

## Abstract

**Background:**

Each year, more than 200 million children under the age of 5 years, almost all in low- and middle-income countries (LMICs), fail to achieve their developmental potential. Risk factors for compromised development often coexist and include inadequate cognitive stimulation, poverty, nutritional deficiencies, infection and complications of being born low birthweight and/or premature. Moreover, many of these risk factors are closely associated with newborn morbidity and mortality. As compromised development has significant implications on human capital, inexpensive and scalable interventions are urgently needed to promote neurodevelopment and reduce risk factors for impaired development.

**Method/Design:**

This cluster randomized trial aims at evaluating the impact of volunteer community health workers delivering either an integrated neonatal survival kit, an early stimulation package, or a combination of both interventions, to pregnant women during their third trimester of pregnancy, compared to the current standard of care in Kwale County, Kenya. The neonatal survival kit comprises a clean delivery kit (sterile blade, cord clamp, clean plastic sheet, surgical gloves and hand soap), sunflower oil emollient, chlorhexidine, ThermoSpot^TM^, Mylar infant sleeve, and a reusable instant heater. Community health workers are also equipped with a portable hand-held electric scale. The early cognitive stimulation package focuses on enhancing caregiver practices by teaching caregivers three key messages that comprise combining a gentle touch with making eye contact and talking to children, responsive feeding and caregiving, and singing. The primary outcome measure is child development at 12 months of age assessed with the Protocol for Child Monitoring (Infant and Toddler version). The main secondary outcome is newborn mortality.

**Discussion:**

This study will provide evidence on effectiveness of delivering an innovative neonatal survival kit and/or early stimulation package to pregnant women in Kwale County, Kenya. Study findings will help inform policy on the most appropriate interventions for promoting healthy brain development and reduction of newborn morbidity and mortality in Kenya and other similar settings.

**Trial registration:**

ClinicalTrial.gov NCT02208960 (August 1, 2014)

## Background

### Early childhood development

Over 200 million children under 5 years of age, the majority of whom reside in south Asia and sub-Saharan Africa, are failing to meet their development potential [1]. Children’s development encompasses several interconnected domains including cognitive, language, motor, social and emotional, and adaptive behaviour. Early child development (ECD) establishes the foundation for wellbeing and productivity throughout the life-cycle. For example, early cognitive impairment is a predictor of poor educational achievements later in life [1, 2]. Children who do poorly in school are less likely to become productive adults; they are more likely to have low incomes, high fertility, and have difficulty in providing adequate care for their children [1]. Thus, compromised development contributes to the propagation and exacerbation of poverty between generations and has implications on social equity and national development. In general, investments in women’s and children’s health yields high rates of return in health, social and economic benefits [3]. Notably, a recent economic simulation study that included 73 low- and middle-income countries (LMICs) estimated that by increasing preschool enrolment, only one component of ECD, by 25 % and 50 %, a total economic benefit of $10.6 and $33.7 billion, respectively, could be achieved with a benefit-to-cost ratio of 17.6 to 1 [4].

The first month of life is an important period in brain development during which there is significant neurogenesis, synaptogenesis, and myelination [1, 5]. Even small perturbations in the early developmental pathway of the brain can have long-term consequences on its strutural and functional capacity, and subsequent child development [5]. Brain development can be affected before and after delivery by both biological and psychosocial factors. Risk factors associated with compromised child development are complex and include poverty, malnutrition, infection, complications due to being born premature or with a low birthweight (LBW) and inadequate cognitive stimulation [6–8]. Since exposure to multiple risk factors increases the likelihood of poor development [9], the coexistence of factors associated with impaired development further exacerbates the problem in LMICs. The importance of promoting healthy brain development and preventing cognitive impairment in LMICs is further underscored by the absence of systems to identify and manage developmental delays soon after onset. Moreover, many risk factors for compromised development, namely infection and complications due to being born LBW and/or premature, are also closely related to newborn morbidity and mortality [10–13]. Newborn deaths account for approximately 40 % of all deaths in children under the age of five [14] and most are largely preventable. Thus, reducing the incidence of insults during the neonatal period has the potential to not only improve newborn survival but also improve long-term developmental outcomes.

A growing body of evidence suggests that early interventions can help prevent or reduce the loss of developmental potential in children [4, 15]. A recent systematic review reported substantial positive effects on child development in most effectiveness studies on ECD conducted in LMICs [4]. Interventions that target parenting and education support, preschool enrolment and programing, and improved maternal and child nutrition have each demonstrated positive effects on development [4, 15]. Interventions that were most effective were those that were comprehensive, engaged younger and disadvantaged children and families, were of adequate duration, intensity, and quality, and were integrated with other interventions including health, nutrition and conditional cash transfer programs [4, 15].

Parenting interventions include promotion of stimulation through responsive and developmentally suitable caregiver-child interactions. Stimulation has been shown to have positive effects on child development in numerous effectiveness studies and can be promoted through home visits, community groups, regular clinic visits, media outlets or through a combination of delivery mechanisms [4]. Delivery of stimulation interventions that focus on only the parent and family or on both the parent and the child has demonstrated positive effects. In rural Pakistan, children who received responsive stimulation delivered by Lady Health Workers, had significantly higher developmental scores on the cognitive, language, and motor scales at 12 and 24 months of age, and on the social-emotional scale at 12 months of age, than those who did not receive responsive stimulation [16]. Similarly, early stimulation among stunted children aged between 9 and 24 months in Kingston, Jamaica had a beneficial and sustained effect on their development at 2 years of age and during adolescence [17, 18]. Despite evidence on the effectiveness of stimulation interventions in early childhood, successful scale-up of programs to sustainably improve child development has been variable [4]. In addition, there are limited data on the effect of parenting interventions that focus on the engagement of pregnant women. Inclusion of pregnant women in early stimulation interventions has shown promise [19] and has been identified as a research area that merits further exploration [4].

Although a relationship between newborn morbidities and impaired cognitive development [6, 10, 20, 21] has been established, there remains a paucity of data on how interventions, that either reduce newborn maladies or facilitate their early detection, impact child development. For example, while numerous controlled studies have reported an association between emollient therapy and reduced risk of infection, improved thermoregulation and growth [22], and reduced newborn mortality in preterm neonates [23], neurodevelopmental outcomes have only been reported in one emollient therapy trial [24]. Of note, the study was limited to assessment of neurobehavioral aspects during the neonatal period and demonstrated no difference between intervention and control groups [24]. In addition, while umbilical cord cleansing with chlorhexidine has been shown to reduce both neonatal mortality and omphalitis/infections [25]; to the best of our knowledge, no studies have explored the effect of chlorhexidine application on developmental outcomes. While several studies have investigated the beneficial effects of Kangaroo Mother Care (KMC) on morbidity and mortality among LBW infants, limited data are available on the association between KMC and long-term developmental outcomes [26, 27]. Given the link between neonatal insults and compromised development, the importance of interventions for the prevention and early detection of newborn illness goes well beyond their effect on short-term health outcomes and newborn survival.

### Child health and development in Kenya

As is the case in most LMICs, Kenya has no data on child development. Using poverty and stunting (height-for-age z-scores below −2 SD from the median of the reference population) as indicators of poor development, the prevalence of disadvantaged children under the age of five in Kenya in 2004 was estimated to be between 40 and 60 % [1].

Stunting in early childhood is caused by poor nutrition, which in itself is often aggravated by infection. Significant associations have also been reported between stunting and developmental delays [7]. Kenya was ranked 47^th^ out of 136 countries with highest prevalence of stunting in 2009 [28]. According to the 2014 Kenyan Demographic Health Survey (KDHS), approximately 25 % of Kenyan children are stunted, while 8 % are severely stunted (height-for age z-scores are below −3 SD from the median of the reference population) [29]. Stunting was noted to be more common among children in rural areas (29 %) compared to those in urban areas (20 %). An inverse relationship was also found between household wealth and child stunting. Stunting in Kenyan children decreases with rising household wealth [29]. In Kenya, associations between height and child development measures [30] as well as socioeconomic status during infancy and cognition at 5 years of age have also been reported [31].

Child mortality rates provide a basic indicator of a country’s socioeconomic level and quality of life. During the 5-year period prior to the 2014 KDHS survey, child, infant and newborn mortality rates were 52, 39 and 22 per 1000 live births, respectively [29], falling short of the country’s Millennium Development Goal 4 (MDG4) targets [32]. While Kenya has experienced a downward trend in under-5 mortality rates since 1998, newborn mortality rates have declined much more slowly. Today, newborn mortality accounts for approximately 40 % of all deaths within the first 5 years of life in Kenya [29].

### Kenyan health system

The Constitution of Kenya, 2010, created a decentralized system of governance that became operational in 2013. In the decentralized structure, selected functions including provision of health care services were devolved to 47 County level governments; County governments are responsible for health facilities, pharmacies, ambulance services, and the promotion of primary health care in their counties [33]. Health service delivery is structured along six tiers of service provision that range from level-1 (community) to level-6 (tertiary referral facilities) [33]. Community-based health services, which comprise basic promotive, preventive and simple curative health, aim to strengthen primary health care at the community level. The building block for level-1 health service provision is the Community Unit where each unit comprises between 5000 and 10,000 people, and served by 50 to 75 community health workers (CHWs) and 1 or 2 community health extension workers (CHEWs). CHEWs are formally engaged, government-paid employees of the health system who, among other tasks, are responsible for providing continuous training and supervision to approximately 50 CHWs. This implies that each CHEW supervises approximately 25 CHWs. CHWs are part-time volunteer workers who act as ‘gate keepers’ of health in the community and are each responsible for providing care to about 20 households. CHWs are connected to primary health facilities through their supervising CHEW. While the existing Community Health Strategy (CHS) is appreciated, high attrition rates, lack of accountability for volunteer CHWs and lack of funds to pay CHW salaries need to be addressed [34].

### Rationale

In order for children to reach their developmental potential, interventions designed to promote development, alongside the prevention and early detection of newborn illness are essential [35]. This study aims to investigate the impact of delivering a neonatal survival kit and/or early cognitive stimulation package, on development at 12 months of age and neonatal mortality.

## Methods/Design

### Objective and hypothesis

The primary aim of this study is to determine whether an integrated neonatal survival kit and/or newborn stimulation package, when delivered to pregnant women during their third trimester of pregnancy by volunteer CHWs, improves developmental outcomes at 12 months of age. Through a reduction in severe infections and improved thermoregulatory care in the first month of life, we hypothesize that utilization of the neonatal survival kit will result in an improvement of at least one standard deviation in development at 12 months of age as measured by the Protocol for Child Monitoring – Infant/Toddler version (PCM-IT) assessment. Moreover, we hypothesize that the combination of both the neonatal survival kit and early stimulation messaging will have an additive effect on development. Secondary objectives are: i) to determine if introduction of the neonatal survival kit reduces all-cause neonatal mortality; ii) explore whether use of the kit is effective in reducing the incidence of omphalitis and/or severe infection, improves caregiver ability to identify hypothermia and/or fever through use of ThermoSpot, and improves identification of low birth weight through use of a handheld scale. The study will also determine if the interventions increase appropriate referral to local health facilities. Finally, the study will assess knowledge, attitudes, and practices of mothers with their newborn and their willingness to use the kit and their capacity to pay for it.

### Study setting

This study is being conducted in Kwale County, which is located in the southern most point of Kenya in the former Coast Province (Fig. 1). Kwale County covers an area of 8270.2 square km, has a total population of 649,931 [36] and is divided into 4 sub-counties namely, Kinango, Lunga Lunga, Matuga and Msambweni. The average temperature in Kwale County is 24.2 °C and the region experiences both dry and wet seasons; the estimated precipitation levels are between 400 mm and 1680 mm per year.

**Fig. 1 Fig1:**
[figure not shown]
Map of the study catchment area in Kwale County, Kenya. The map image was adapted with permission from https://commons.wikimedia.org/w/index.php?curid=28868036. By Nairobi123 - Own work, CC BY-SA 3.0

Within Kwale County, there are 3 government hospitals, 2 private hospitals, 8 health centres and 64 dispensaries; the average distance covered to reach the nearest health facility is 7 km [36]. Vast distances, a poor network of roads and limited access to motorized transportation for many make it difficult to access health care facilities. In spite of government emphasis on the promotion of facility deliveries, more than 60 % of women in Kwale County still deliver at home without the assistance of skilled birth attendants [37]. The estimated under-five mortality rate in Kwale County, 149 deaths per 1000 live births, is higher than the national average, 116 deaths per 1000 live births [36]. Similarly, neonatal mortality rates in the rural areas of Kwale County are believed to be approximately double the national average of 22 per 1000 live births [29].

In this trial, participant recruitment, informed consent, newborn enrolment and data collection take place in the rural communities surrounding 13 dispensaries in Kwale County (Fig. 1). The average catchment population surrounding each dispensary is ~7500 individuals.

### Design and cluster definition

This community-based study is a cluster randomized controlled, pragmatic, open label intervention trial with four trial arms: neonatal survival kit; stimulation messaging; combination of neonatal survival kit with stimulation messaging; and control (current standard of care in Kwale County [38]) (Fig. 2). A cluster is defined as a single CHW, where each CHW is responsible for the provision of basic health promotion and disease prevention services to approximately 20 households. Within one village, the distance between homes covered by one CHW can be large. Geographic distance thus minimizes any unintended diffusion of arms of interventions between households, especially those serviced by different CHWs (clusters).

**Fig. 2 Fig2:**
[figure not shown]
Schematic diagram of trial activities

### Interventions and comparator

To facilitate future scale-up efforts, the delivery of each intervention was built into the country’s existing health system infrastructure. CHWs routinely conduct home visits to pregnant women during their third trimester of pregnancy, and post-delivery during the first week of life and again 4–6 weeks post delivery. Specifically, the timing of intervention delivery coincides with the existing schedule of CHW home visits. In this trial, a trained study worker accompanies CHWs to their third trimester home visit, explains the study to potential participants, and seeks informed written consent. After obtaining consent, CHWs deliver the appropriate intervention(s) and corresponding education to enrolled pregnant women. In control clusters, CHWs deliver the current standard of community-based pre-natal care in Kenya [38].

The integrated neonatal survival kit comprises a clean birth kit, 4 % chlorhexidine solution, sunflower oil emollient, ThermoSpot™, Mylar infant sleeve, and a reusable, instant heat pack (Fig. 3). In addition, CHWs in the intervention groups are also supplied with a handheld battery-operated weighing scale with a suspended sling to weigh newborns (Fig. 3). A detailed description of each kit component, its intended utilization and associated evidence has been published elsewhere [39].

**Fig. 3 Fig3:**
[figure not shown]
Integrated neonatal survival kit contents. **a** The neonatal survival kit includes: i) clean delivery kit, ii) 4 % chlorhexidine solution that is to be applied with iii) cotton balls, iv) sunflower oil emollient, v) ThermoSpot, vi) a reusable instant heat pack, and vii) a Mylar infant blanket. **b** A handheld battery operated weighing scale will be provided to CHWs in the intervention cluster

The newborn cognitive stimulation program focuses on teaching three key messages to enhance the caregivers’ current practices including: making eye contact and talking to their children; engaging in responsive feeding and caregiving; and singing songs, including those with gentle touch (Table 1). The cognitive stimulation program was adapted from the UNICEF and WHO Care for Child Development package [40], which promotes the appropriate use of communication and play activities by guiding caregivers to be sensitive and responsive to signals from their child. CHWs teach caregivers to integrate each stimulation message into daily activities (e.g., during feeding, bathing, bedtime routines). Three fifteen-minute sessions take place in the homes of participants. At the first visit during the third trimester visit, caregivers are given a locally developed one-page pictorial brochure to act as a memory aid. CHWs describe the messages verbally as participants follow along with the pictorial illustrations of behaviors associated with each of the key messages. The information is re-iterated by CHWs at subsequent routine visits during the first week of life, and at the four to six week follow-up visit. At post-natal visits, CHWs provide modeling, coaching and support while encouraging caregivers to practice the behaviors associated with the three key messages.

**Table 1 Tab1:** Cognitive stimulation messages

Key message
Making eye contact and talking to their children • Encourage caregivers to look into baby’s eyes, smile and talk/sing to their baby • Provide ways for child to see, hear, move their arms and legs freely, and touch (e.g., Caregivers are taught to slowly move colorful objects in front of the child) • Caregivers are taught to not cover the child’s face for long periods of time
Responsive feeding and caregiving
• Teach caregivers that children learn to communicate their needs through movements, sounds and cries. For example, children show interest in breastfeeding by becoming fussy, sucking their hand, or moving their heads toward the breast. • Caregivers are taught to emulate the child’s movements and sounds. Copying the child’s sounds and movements helps caregivers pay closer attention to the child. By imitating the child’s sounds, or movements, the child will often then repeat the activity, in order to get the caregiver to respond again. This increases the child’s attempts to make sounds and move, and the caregiver’s pleasure.
Singing songs, including those with gentle touch
• Encourage the use of core songs based on cultural practices and accompany each by gentle touch • Caregivers are taught that skin-to-skin contact is good and they are encouraged to gently soothe, stroke and hold the child

### Sample size and power estimation

Based on an estimated live birth rate of 39 per 1000 population, baseline NMR of 44 per 1000 live births, and approximately 5 live births per cluster (personal communication [name]), the randomization of 689 CHWs (clusters), with a 25 % chance of being randomized to any one of the four groups (neonatal survival kit, stimulation, neonatal survival kit and stimulation arm, and control), with 90 % enrollment of eligible mothers and including up to a 10 % loss to follow up will provide >90 % power to detect a one standard deviation difference in PCM-IT scores and >80 % power to detect a 40 % reduction in mortality between any two of the four groups. To ensure that randomization was unbiased, a scientist who is not directly involved in the research project performed the cluster randomization. CHWs were trained on the delivery of their randomly assigned intervention at a 1-day intervention-specific workshop; training included specific instructions for CHWs to restrain from sharing their intervention- or trial-specific knowledge with individuals outside their assigned households.

All pregnant women who intend to give birth and permanently reside in the trial catchment area for at least 12 months after delivery and their home or facility-born live births are eligible for enrollment in this study. Enrolment will take place over a period of 12 months targeting a final sample size of 3000 newborn-mother pairs. The first pregnant woman was recruited on November 24^th^, 2014 and the first newborn enrolled on November 28^th^, 2014.

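### The claimed power above 80 % for a 40 % mortality reduction between any two arms does not follow from the stated inputs, which give about 43 to 51 % pairwise

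*Protocol article*

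**What the plan says.** Under Sample size and power estimation, one sentence lists the inputs and draws the conclusion. It assumes a "baseline NMR of 44 per 1000 live births", "approximately 5 live births per cluster" and 689 clusters, each "with a 25 % chance of being randomized to any one of the four groups". It also assumes that 90 % of eligible mothers enrol and that at most 10 % are lost. From these it claims power above 80 % for a 40 % "reduction in mortality between any two of the four groups". The next paragraph describes enrolment over 12 months, "targeting a final sample size of 3000 newborn-mother pairs". No significance level, sidedness, intracluster correlation or design effect is given.

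The Abstract names newborn mortality as the main secondary outcome. Secondary objective (i), under Objective and hypothesis, asks whether the kit reduces it. The Data analysis plan compares survival across the four arms by Cox regression and describes no pooled contrast.

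**The concern.** The wording describes a comparison of one arm with one other arm, with the enrolment and loss allowances already counted. With about 700 newborns per arm and a baseline risk of 4.4 %, only about 49 deaths are expected in any such pair. That is far too few for 80 % power at a 40 % reduction.

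The figure matters for how the mortality result is read. If pairwise power is below or near one half, a true 40 % reduction would be missed about as often as it was found, or more often. A non-significant contrast set beside a published figure above 80 % could then be taken as evidence against an effect of that size. The article says that its findings are meant to inform policy on the kit.

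**Working it through.** **Inputs** (Sample size and power estimation)

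- Control risk p1 = 0.044. A 40 % reduction gives p2 = 0.6 × 0.044 = 0.0264, a difference of 0.0176.
- 689 clusters / 4 = 172.25 per arm. At 5 births each this is 861 births per arm.
- After 90 % enrolment: 861.25 × 0.9 = 775. After 10 % loss: 775.1 × 0.9 = 698.
- From the enrolment target: 3000 / 4 = 750 per arm.
- Assumed: two-sided 5 % and intracluster correlation 0. The second assumption favours the protocol.

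**Formula** (two-proportion z-test, mean risk p̄ = 0.0352)

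- SE0 = √(2 p̄(1 − p̄)/n) = √(0.067922/n)
- SE1 = √((p1(1 − p1) + p2(1 − p2))/n) = √(0.067767/n)
- Power = Φ((0.0176 − z × SE0)/SE1)

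**Stated inputs, one arm against one arm, n = 698**

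SE0 = 0.00986 and SE1 = 0.00985. Then (0.0176 − 1.96 × 0.00986)/0.00985 = −0.176, and Φ(−0.176) = 0.430. The stated figure above 80 % is not reproduced.

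**Other readings of the pairwise sample size**

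| Newborns per arm | Basis | Two-sided 5 % | One-sided 5 % |
|---|---|---|---|
| 698 | both deductions | 43.0 % | 55.5 % |
| 750 | 3000 / 4 | 45.6 % | 58.1 % |
| 775 | enrolment deduction only | 46.8 % | 59.3 % |
| 861 | no deductions | 50.9 % | 63.2 % |
| 951 | 13 dispensaries × 7500 × 0.039 / 4, no deductions | 54.9 % | 66.9 % |

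At 698 per arm, a log-rank (Schoenfeld) calculation gives 43.2 % and simulated Fisher exact tests about 37 %. Even a one-sided 10 % test at 951 per arm reaches only 78.9 %.

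**Clustering.** With 5 × 0.81 = 4.05 newborns per cluster, the design effect is 1 + 3.05 × ICC. At 698 per arm an assumed ICC of 0.01 gives 42.0 %, and 0.05 gives 38.3 %.

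**Required size for 80 % power**

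n = (1.960 × √0.067922 + 0.842 × √0.067767)² / 0.0176² ≈ 1,720 per arm. That is about 121 deaths per pair (1,720 × 0.0704), against an expected 698 × 0.0704 = 49.

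**Detectable reduction at 80 % power, two-sided.** It is 59.1 % at 698 per arm and 54.1 % at 861, so roughly 55 to 60 %.

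**Two arms pooled on each side**

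- No deductions, 689 × 5 / 2 = 1,722 per side: 80.0 % two-sided.
- Both deductions, 1,722.5 × 0.81 = 1,395 per side: 71.3 % two-sided and 81.0 % one-sided. About a 44 % reduction is detectable at 80 % power two-sided.

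**The case against.** Several points on the other side are fair. Alpha and sidedness are not stated, so two-sided 5 % is an assumption. The 10 % loss is a ceiling, so 698 is the low end and a range is fairer than a single figure. Mortality is a secondary outcome. The primary power claim, one standard deviation on the developmental score, is untouched: about 22 children per arm give 90 % power before any design effect. Whoever interprets a null result would also have the confidence interval. None of this brings a pairwise comparison to 80 %.

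A reader might go further in three ways that the document does not support.

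- **That the calculation was really done on pooled arms.** The closeness of 1,722 to the required 1,720 is suggestive, but the article never says so. Nor is that the only pooled route to the figure, since a one-sided pooled test also exceeds 80 % after both deductions. How the figure arose remains conjecture.
- **That the target of 3000 is a second arithmetic error.** The sentence is about enrolment, and 3,445 × 0.9 gives about 3,100 enrolled. A rounded target about 3 % below an approximate product is not a contradiction.
- **That 44 per 1000 is too high, so that power is lower still.** Study setting says that neonatal rates in rural Kwale "are believed to be approximately double the national average of 22 per 1000 live births", which agrees with 44. Applying the county-to-national ratio of under-five mortality to the neonatal rate would move a ratio between different outcomes and sources.

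Requiring a pooled kit against no-kit analysis would also overreach. It suits secondary objective (i), but the Data analysis plan treats the arms separately, and a pooled kit effect is simple to interpret only if stimulation does not modify it.

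**Conclusion.** Wrong as written. On the protocol's own inputs, power for a 40 % mortality reduction between two single arms is about 43 % with the stated enrolment and loss, and 51 % with no losses at all. These figures assume a two-sided 5 % test and no design effect; any positive intracluster correlation lowers them. A one-sided 5 % test gives 56 to 63 % over the same range. The shortfall does not depend on the unstated alpha or on rounding of the cluster size, because the required sample is about 2.5 times the stated one (1,720 / 698). The conclusion is limited to the pairwise mortality power statement. It does not touch the primary outcome, the enrolment target or the baseline rate.

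**What to change.** In Sample size and power estimation, remove the power figure above 80 % for mortality between any two arms. State instead that pairwise power for a 40 % reduction is about 43 to 51 %, depending on enrolment and loss, and that about a 55 to 60 % reduction is detectable with 80 % power. Give the alpha, its sidedness and any design effect used.

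If the authors intended the two kit arms against the two arms without the kit, they should say so before analysis. They should then state about 71 % power after the stated losses (about 1,395 newborns per side), with 80 % power for about a 44 % reduction, two-sided 5 % and no design effect. They should also bring the Data analysis plan into line. That choice is theirs.

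The cost is wording and a less favourable stated power. No extra enrolment is needed.
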